### Baseline interview

Upon patient recruitment and allocation to groups, a one-on-one baseline interview and evaluation will be conducted to (1) record patients’ comprehensive medical history; (2) assess patients’ nutritional states; (3) assess patients’ functional capacity during the 6-min walk test (6MWT); (4) conduct a pulmonary function test (Spirodoc portable pulmonary function meter, Medical International Research S.r.l., 09,000,261,972), during which the forced expiratory volume in 1 s (FEV1, L), FEV1%, forced vital capacity (FVC, L), FVC%, FEV1/FVC, peak expiratory flow (PEF, L/s), and PEF% will be recorded; (5) record laboratory results, if applicable, including the levels of alanine transaminase (ALT), creatine (CR), C-reactive protein (CRP), albumin (Alb), glucose (Glu), and myocardial enzymes; (6) evaluate the patients’ baseline quality of life and mental state using standard tools [hospital anxiety and depression scale (HADS), World Health Organization disability assessment schedule II (WHODAS 2.0) score, postoperative quality of recovery score-15 (QoR-15)]; (7) explain in detail the prehabilitation plan for both groups; and (8) encourage patients to choose a preferred way to be followed up, such as by telephone, short text messages, or WeChat messaging.

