### Outcomes

The primary outcome will be the perioperative 6MWD (baseline, 1 day presurgery, and 30 days postsurgery). The 6MWT will be conducted following the guidelines of the American Thoracic Society (ATS) [17]. The research staff members who will be involved in performing the 6MWT will all be trained before administering this test. We will conduct the 6MWT indoors in a 30-m-long corridor in PUMCH. We will ensure that supplies needed for safety issues are readily available whenever the 6MWT is performed, including oxygen, sublingual nitroglycerine, aspirin, and albuterol. All the staff members who will be involved have been previously certified in cardiopulmonary resuscitation. The 6MWT will be conducted in a standard manner. From the 10-min rest period before the test to all the verbal instructions provided to the patients before and during the test, all procedures will be performed in accordance with the standard ATS guidelines.

We will record the patients’ sex, age, height, weight, medications before the test, and whether they need oxygen supplementation during the test. We will measure blood pressure, HR, oxygen saturation, and the Borg RPE score before and after the test. We will note the number of laps and calculate the 6MWD.

The secondary outcomes will include the perioperative pulmonary function test results, including the FEV1, FEV1%, FVC, FVC%, FEV1/FVC, PEF, and PEF% values (baseline, 1 day presurgery, and 30 days postsurgery); the perioperative HADS and WHODAS 2.0 (baseline, 1 day presurgery, and 30 days postsurgery); post-surgery QoR-15 (3 consecutive days after surgery); prognostic information (mortality and morbidity, length of hospital stay, ICU stay time, duration of chest tube placement duration); and perioperative laboratory results, if applicable, including the levels of ALT, CR, CRP, Alb, Glu, and myocardial enzymes (baseline, 1 day presurgery, and 30 days postsurgery).

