### Statistical analysis

Patients’ baseline characteristics will be described by descriptive analysis and compared between the groups to detect clinically relevant differences. If evident baseline imbalance exists, the analysis of the primary outcome will be adjusted. For tests conducted perioperatively including 6MWD, pulmonary function test results, HADS and WHODAS 2.0 score, a linear mixed-effects model will be built to analyze the interaction between intervention and time [18]. Other secondary outcomes including the QoR-15 score, length of hospital stay, chest tube duration, and postoperative complications will be analyzed using *χ*^2^ test and the Mann–Whitney *U* where appropriate. Patients lost to follow-up will be considered as non-adherence. We will perform sensitivity analysis to test if the analyses of the primary outcome will be robust to the missing values. All statistical analyses will be completed in R (R Foundation for Statistical Computing, Vienna, Austria; version 3.5.2).

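### QoR-15 is collected at baseline and on three postoperative days, but its stated rank test takes one value per patient and no day or summary is named

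*Protocol article*

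**What the plan says.** Four statements in the protocol article bear on this.

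- **Baseline interview**, item 6: the research team will "evaluate the patients’ baseline quality of life and mental state using standard tools", and the tools listed include QoR-15. A pre-intervention value therefore exists for each patient.
- **Outcomes**: the secondary outcome is "post-surgery QoR-15 (3 consecutive days after surgery"), that is, three further values per patient.
- **Statistical analysis**, on method: for 6MWD, pulmonary function, "HADS and WHODAS 2.0 score, a linear mixed-effects model will be built to analyze the interaction between intervention and time". QoR-15 is not in that list. It comes in the next sentence: "Other secondary outcomes including the QoR-15 score, length of hospital stay, chest tube duration, and postoperative complications will be analyzed using" the chi-square test and the Mann–Whitney U test, whichever fits.
- **Statistical analysis**, on baseline: "If evident baseline imbalance exists, the analysis of the primary outcome will be adjusted". Nothing comparable is said for any secondary outcome.

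The article does not say which QoR-15 value enters the test: a particular day, a mean over days or a change from baseline.

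**The concern.** The named test and the collected data do not fit together. Length of stay and chest tube duration give one number per patient, and Mann–Whitney suits them. QoR-15 gives four. To apply a two-sample rank test, someone must first reduce those four values to one or run the test more than once, and the article does not say how.

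Two things are at stake. The first is precision: two further postoperative days and a baseline score would be paid for in patient and staff time and then not used in the comparison. The second is freedom of choice: an unnamed day or summary can be settled after the results are visible. By the schedule in the Outcomes section, QoR-15 is the only questionnaire taken in the first three days after surgery, so no other score covers that period.

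**Working it through.** The article states no effect, standard deviation or correlation for QoR-15, so there is no figure of the plan's own to reproduce. The calculation below shows what the unused data could be worth.

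**Inputs**
- From the article: one baseline value, three postoperative values, two equal groups, two-sided 5% level, 45 evaluable patients per group (Sample size section).
- Assumed: equal variance on each day (set to 1), a common between-day correlation rw of 0.5–0.7, and the same correlation rb of 0.3–0.5 between baseline and each day. Wider values are shown as a check.

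**Variance**
- Single day, unadjusted: 1.
- Mean of three days: m = (1 + 2·rw)/3.
- Mean of three days, adjusted for baseline: v = m − rb².

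**Power**, for an assumed true difference of 0.5 SD on every day: Φ(0.5/√(2v/45) − 1.96). For a single-day Mann–Whitney test, v = 1/0.955, from its asymptotic efficiency under normality.

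| rw | rb | m | v (single day = 1) | v/m | Power |
|---|---|---|---|---|---|
| 0.5 | 0.5 | 0.667 | 0.417 | 0.625 | 96% |
| 0.5 | 0.3 | 0.667 | 0.577 | 0.865 | 88% |
| 0.7 | 0.5 | 0.800 | 0.550 | 0.688 | 89% |
| 0.7 | 0.3 | 0.800 | 0.710 | 0.888 | 80% |
| 0.5 | 0 | 0.667 | 0.667 | 1 | 83% |
| 0.7 | 0 | 0.800 | 0.800 | 1 | 75.5% |
| 0.8 | 0 | 0.867 | 0.867 | 1 | 72% |

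Worked example, rw = rb = 0.5: m = (1 + 1)/3 = 0.667; v = 0.667 − 0.25 = 0.417; √(2 × 0.417/45) = 0.136; 0.5/0.136 − 1.96 = 1.71; power 96%.

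Single-day Mann–Whitney: √(2 × 1.047/45) = 0.216; 0.5/0.216 − 1.96 = 0.36; power 64%.

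The first four rows give the main range: 42–71% of the single-day variance and 63–89% of the variance of the unadjusted three-day mean. The last three rows set the baseline correlation to zero. There the whole gain comes from averaging days.

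**If each day were tested separately at 5%**, the chance of at least one false positive would be 1 − 0.95³ = 14.3% for independent days. Days within a patient are not independent. Simulating three correlated normal test statistics (one million draws) gives 12.5% at correlation 0.5 and 10.9% at 0.7.

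**The case against.** The strongest reply is that nothing here is invalid. Under randomisation, a Mann–Whitney comparison of a postoperative score is a sound test, and a rank method is a reasonable choice for a bounded score that may be skewed after surgery. It could also be applied to a three-day mean or a change from baseline, and a fuller document might say so. All of that stands. The point is therefore about precision and an unspecified input, not about error. It survives because the article itself fixes the method for QoR-15, and a mean or change score is something a reader would have to supply.

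Some stronger readings are tempting but are not supported:

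- *QoR-15 has the same structure as HADS and WHODAS 2.0 and was left out of their model by oversight.* Those two are measured at baseline, the day before surgery and 30 days after. QoR-15 as an outcome is postoperative only, on three adjacent days. The separate handling follows that schedule, and adding QoR-15 to the same model would mix two time axes.
- *Three uncorrected tests are planned.* The article does not say that each day will be tested, so the 11–12.5% is conditional on a choice not stated.
- *No effect estimate or interval will be given.* The article names tests and is silent on reporting. A rank test can be accompanied by a location-shift estimate with a confidence interval.
- *A chi-square test will be applied to the score.* The sentence covers several outcomes, and chi-square plainly belongs to complications.
- *QoR-15 is the main early-recovery outcome.* The Outcomes section gives the secondary outcomes no ranking.

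The size is also open to challenge. Baseline is recorded before a prehabilitation period of 2 to 4 weeks and the operation itself, so its correlation with days 1–3 could fall below 0.3. In that case the gain shrinks towards that from averaging alone.

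**Conclusion.** The point holds as a matter of efficiency and clarity. As written, the QoR-15 comparison uses neither the baseline value nor the repeated measures, and it leaves the choice of day or summary open. Under the assumed correlations, the data already collected would cut the variance to 42–71% of that of a single-day comparison. At the pessimistic end of the wider range (between-day correlation 0.8, no baseline correlation), the improvement is modest: 72% against 64% power for a 0.5 SD difference. These figures rest on assumed correlations, equal variances and an effect that is the same on each day; none comes from the article. The outcome is secondary, the rank test remains valid, and the 6MWD conclusion is untouched.

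**What to change.** Take QoR-15 out of the Mann–Whitney sentence and give it a linear mixed model of its own, separate from the model for baseline, presurgery and day 30:

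- outcome: QoR-15 on postoperative days 1, 2 and 3, with day as a categorical factor;
- fixed effects: group, day and group-by-day, with baseline QoR-15 as covariate;
- random effect: patient;
- single reported contrast: the group difference averaged over days 1–3, with its 95% CI;
- sensitivity analysis: a Mann–Whitney test of the three-day mean, in case the score is markedly skewed.

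Length of stay and chest tube duration can stay with Mann–Whitney.

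The cost is a sentence or two in the analysis section and no new data. The Trial status section already provides a route for reporting changes to the statistics plans, and the change should be made before outcome data are examined. There are two small downsides. A linear model makes a distributional assumption for a bounded score, which the sensitivity analysis addresses. The Baseline interview section also places the interview after allocation, so the covariate should be the score taken before the programme is explained to the patient, as the order of its items suggests.

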## Dissemination plans

The final trial dataset will be available on the online platform of the Chinese Academy of Medical Sciences, the sponsor. As this trial is unicentral, the main researchers will also have full access to the final trial dataset. Any data required to support the protocol can be supplied on request. We plan to communicate trial results thoroughly with our multidisciplinary team and encourage conversations with medical providers in other state facilities during the annual conference of the Chinese Medical Association. These medical providers will in turn disseminate results to the patient community. We will also inform the patient community of the results during pre-surgery evaluation and consults. We are planning to invite researchers from our multidisciplinary team as co-authors in the publication process, and we are not planning to use professional writers. For further dissemination of the results, we will post the study concept and major results on the website of the anesthesiology department of PUMCH. We will be open to provide the whole study protocol as well as the patient-level dataset when approached by interested health providers or researchers.

## Trial status

This manuscript is based on version 2.1 of our study protocol, updated on July 22, 2020. Enrollment started on November 9, 2019, then went on pause during January 2020 due to the COVID-19 pandemic. Since then, there were three spells of pandemic outbursts resulting in tightened restrictions on traveling and hospital admission policies, and recruitment was put on halt during those periods. Completion of recruitment is expected to be in November 2023. If there will be important modifications to protocols related to enrolment, prehabilitation strategies, outcomes, and statistics plans, we will inform all researchers and DMC members, report to our Institutional Review Board, and make timely updates on ClinicalTrials.gov and related journals.

## Discussion

The Prehabilitation in Thoracic Surgery Study investigates two types of prehabilitation strategies in patients undergoing VATS, a potentially more promising multimodal strategy and a more recognized aerobic exercise strategy, to answer the question of whether the former is more beneficial than the latter.

As gastrointestinal cancer is the most extensively explored condition regarding prehabilitation, there is a large amount of evidence showing that a multimodal strategy is more beneficial than a unimodal strategy in improving functional capacity recovery postsurgery. Our group formerly conducted a trial demonstrating that a short-term home-based multimodal prehabilitation strategy improves postsurgical 6MWD, a well-established marker for functional capacity. Most of the studies on prehabilitation in VATS patients included unimodal strategies, and aerobic exercise is widely considered to be the most important factor. We hope this study will shed more light on the differences in prehabilitation strategies in VATS patients.

This study is a pragmatic trial, and we made an effort to create a feasible and flexible protocol tailored to patients’ individual needs and preferences to promote adherence to training strategies and achieve viable, effective prehabilitation outcomes that will adapt to real-world clinical practice. The eligibility requirement of this trial consists of a wide range of patients’ characteristics, excluding mainly patients who are deemed unable or unsafe to perform the 6-min walk test and the prehabilitation program unsupervised due to serious comorbid conditions. The types of aerobic exercise, the elasticities of the pulling straps used in resistance training, and components in the psychological therapy are chosen by patients to facilitate adherence and ensure safety. Patient interviews make up a crucial part of the study, as they ensure patient safety and the fidelity of protocol adherence data and allow valuable feedback to be collected.

The training protocols for both arms were refined based on feedback from patients and multidisciplinary investigators during our previous study, so the strategy is more patient-centered and efficient. We propose a mixed methods evaluation panel to further assess the efficacy and feasibility of a multimodal prehabilitation strategy compared to aerobic training alone within a thoracoscopic surgery setting. We hope this study will provide more evidence on the prehabilitation methods within the thoracic surgery community and help promote better and faster functional recovery.

## Data Availability

Not applicable.

## Abbreviations

VATS: Video-assisted thoracoscopic surgery
PUMCH: Peking Union Medical College Hospital
6MWD: 6-Min walk distance
NSCLC: Non-small cell lung cancer
PPCs: Postoperative pulmonary complications
ASA: American Society of Anesthesiologists
6MWT: 6-Min walk test
FEV1: Forced expiratory volume in 1 s
FVC: Forced vital capacity
PEF: Peak expiratory flow
ALT: Alanine transaminase
CR: Creatine
CRP: C-reactive protein
Alb: Albumin
Glu: Glucose
HADS: Hospital Anxiety and Depression Scale
WHODAS 2.0: World Health Organization Disability Assessment Schedule II
QoR-15: Postoperative Quality of Recovery Score-15
RPE: Rating of perceived exertion
HR: Heart rate
ATS: American Thoracic Society
SD: Standard deviation
CBC: Complete blood count
CRF: Case report form
DMC: Data Monitoring Committee
